## Background

As of 2021, the worldwide average cesarean section rate was 21 %, and is predicted to increase to 30 % by 2030 [1]. In 2022, 39 % of babies in Australia and 32.1 % in the United States (US) were born by cesarean delivery [2,3]. Occurring in parallel is the obesity epidemic, with 61 % and 69 % of women in Australia and the US, respectively, living with overweight or obesity [4]. Obesity is a major risk factor for cesarean section, and higher risk of complications of the surgery including wound infection and longer hospital stay [5,6]. Cesarean delivery is in turn associated with greater risk for mothers and babies including maternal death, severe postpartum haemorrhage, endometritis [7,8], as well as complications for future pregnancies, such as preterm birth and abnormal placentation [9].

Interventions to reduce perinatal complications have focused on gestational weight gain (GWG), with studies linking it to adverse pregnancy outcomes, including cesarean delivery [[10], [11], [12]]. Excessive GWG is defined according to prepregnancy body mass index (BMI) by both the National Academy of Medicine (NAM) and the World Health Organization with lower GWG recommended for those starting pregnancy with a BMI in the obese category compared to those with normal BMI at the start of pregnancy [13,14]. Studies to date have included adjustment for pre-pregnancy or early pregnancy BMI, but, it is unknown whether this association could in fact be mediated by increased BMI at the time of delivery. Recently there has been some questioning of the value of GWG as a useful measure to predict obstetric outcomes. In a study by Dodd et al that used data from 20 randomized controlled trials, the authors identified a meaningful relationship between maternal BMI and GWG, whereby GWG decreased with increasing BMI. They also demonstrated a relationship between BMI and adverse pregnancy outcomes, whereby the risk of adverse pregnancy outcomes increased with increasing maternal BMI. However, they found no evidence that the effect of maternal BMI on outcomes is via an effect on GWG. That is, gestational weight gain may not be associated with cesarean delivery independently of BMI at the time of birth [16].

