Given that finding, in this research we sought to explore whether using gestational BMI change is a better measure to use in understanding adverse obstetric outcomes. The primary objective of this study is to describe the relationship between gestational BMI gain and cesarean delivery and to compare pre-pregnancy BMI versus BMI at the time of birth as predictors of cesarean delivery.

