### Primary study factors

-Change in maternal BMI from pre-pregnancy to birth-Maternal BMI (either pre-pregnancy BMI or BMI at birth as outlined below)

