### Analysis plan

Data will be downloaded from the CDC website (https://www.cdc.gov/nchs/data_access/vitalstatsonline.htm) for the most recent year with available data (2023 at the time of writing this protocol).

If data missingness for one or more explanatory or outcome variables occurs in > 5 % and < 40 % eligible births then multiple imputation will be considered. Potential mechanisms of missingness and the relationship of missingness to the outcome and covariates will be assessed when deciding to conduct multiple imputation or a complete case analysis.

If multiple imputation is required, we will use fully conditional specification with five imputed datasets. Any multiple imputation will include all explanatory and outcome variables, and any interaction terms. Interdependencies amongst variables will be handled with the passive imputation method. P-values for the likelihood ratio test for each variable in each imputed dataset will be pooled using the median p-value rule.

Using Robust Poisson Regression, maternal pre-pregnancy BMI will be modelled on the primary outcome of cesarean delivery and other covariates (listed below) excluding BMI gain during pregnancy. Maternal BMI at the time of delivery will be modelled on the same covariates. Of these two models, the model with the lowest Akaike Information Criterion (AIC) will be used to select the BMI variable with the greatest explanatory power to be used in subsequent analyses (either pre-pregnancy or delivery BMI). This variable is referred to as ‘Maternal BMI’ in all subsequent analyses below. The two models will also be compared using the log-likelihood test.

Pre-pregnancy BMI will be categorized according to the United States Centers for Disease Control and Prevention which classifies adult BMI as underweight (BMI < 18.5), normal weight (BMI 18.5 – 24.9), overweight (BMI 25-19.9), Class 1 obesity (BMI 30-34.9), Class 2 Obesity (BMI 35-39.9), and Class 3 Obesity (BMI 40 or more) [20]. Delivery BMI will be classified such that the same numbers of women will be in each class (i.e., the same quantile cut-offs will be used for pre-pregnancy and delivery BMI groups). This is expected to account for weight gain in pregnancy including factors such as fetal weight and amniotic fluid volume. Based on the exploratory analysis for 2022 data, BMI gain and gestational weight gain will be treated as linear splines with one knot placed at 5 kgm^-2^ and at 12 kg respectively.

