As nulliparous women are an important group who contribute to the first/primary cesarean delivery rate, we will test for interaction (effect modification) between maternal BMI gain and parity, and maternal BMI and parity. If interaction is present (BMI or BMI gain have a different association with cesarean delivery depending on parity), then the primary analysis will be restricted to nulliparous women only and we will conduct secondary analyses for parous women.

For the primary outcome of cesarean delivery, backward stepwise Robust Poisson Regression will be used. The following variables will be included in the multivariable Poisson regression model as potential predictors of cesarean section:•Maternal BMI (not eligible for exclusion in the backwards stepwise regression).•Gestational BMI gain (not eligible for exclusion in the backwards stepwise regression)•Parity•Maternal age (continuous)•Gestational age•Maternal height•Maternal race•Cigarette smoking•Payment type•Trimester of onset of maternity care (4 categories: first, second or third trimester, or no•antenatal care)•Education (categorized)•Fertility treatment used•Diabetes (3 categories: pre-pregnancy, gestational, none)•Hypertension in pregnancy (dichotomous)•Interaction terms: BMI x parity and BMI gain x parity

Birthweight will not be included as an explanatory variable because it was considered that fetal weight may be on the causal pathway between BMI or BMI gain and cesarean delivery. Therefore, the relative risks for BMI or BMI gain for the primary outcome of cesarean delivery will include any indirect effect mediated through fetal weight.

If Robust Poisson Regression Models do not converge then alternative regression methods will be considered.

For secondary outcomes, all explanatory variables will be retained in the model. Stepwise backward regression will not be used. No interaction terms will be used.

For the secondary outcome of third or fourth degree perineal laceration, the data will be limited to vaginal births only and the following covariates will be used: BMI at delivery, BMI gain, parity, maternal age, gestational age, maternal height, maternal race, mode of delivery (unassisted/vacuum/forceps).

For the secondary outcome of trial of labour, the following covariates will be used: BMI at delivery, BMI gain, parity, maternal age, gestational age, maternal height, maternal race, payment type, education, trimester of onset of maternity care, use of ARTs, and gestational diabetes.

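### An AIC comparison of models without BMI gain decides whether the gain relative risk is adjusted for pre-pregnancy or delivery BMI, and so decides what that relative risk means

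*Protocol article*

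**What the plan says.** All references are to the Protocol article.

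- **Objective (Background).** There are two parts. The first reads "The primary objective of this study is to describe the relationship between gestational BMI gain and cesarean delivery". The second sets the two BMI measures against each other for predicting the outcome.
- **Exposure (Primary study factors).** Gain is the "Change in maternal BMI from pre-pregnancy to birth".
- **Selection (Analysis plan).** Two robust Poisson models are fitted, one per BMI measure, "excluding BMI gain during pregnancy". Then "the model with the lowest Akaike Information Criterion (AIC) will be used to select the BMI variable with the greatest explanatory power". The winner is named Maternal BMI and carried into every later analysis.
- **Primary model (Analysis plan).** Maternal BMI is forced in, and so is "Gestational BMI gain (not eligible for exclusion in the backwards stepwise regression").
- **Secondary models (Analysis plan).** The laceration model lists "BMI at delivery, BMI gain, parity, maternal age, gestational age, maternal height, maternal race, mode of delivery (unassisted/vacuum/forceps"). The trial-of-labour model also names BMI at delivery together with gain.
- **Subgroup analyses.** The trial-of-labour subgroup uses whichever BMI variable the main analysis chose.
- **Sensitivity analysis.** Weight gain replaces BMI gain, and a complete-case refit follows any imputation. Neither refits the gain model with the BMI variable that lost.

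**The concern.** Holding pre-pregnancy BMI fixed, one more unit of gain is simply one more unit gained. Holding delivery BMI fixed, one more unit of gain also means one unit less before pregnancy. These are different contrasts, and the plan would report either one as the relative risk for gestational BMI gain, depending on an AIC difference. AIC ranks predictive fit and cannot say which contrast the objective needs.

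The selection is also not neutral. Gain is left out of both candidate models, so delivery BMI has an advantage when gain does predict cesarean, because it carries gain inside it. Once selected, it is paired with gain and takes over part or all of gain's coefficient.

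Two other parts of the plan fit badly with this. Birthweight is excluded because it may lie between gain and cesarean. Delivery BMI, which the Background itself raises as a possible mediator, may nevertheless enter. The fixed use of delivery BMI for laceration and trial of labour also conflicts with the rule that the selected variable serves all later analyses.

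At stake is the interpretation. The section Uniqueness of the study says the work will explore whether BMI rather than weight gain is linked to cesarean birth. A gain estimate near 1 could be read that way although gain has its full planned effect.

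**Working it through.** **1. The plan's own figures.** The target is one percentage point per unit of gain. For nulliparous women this is 28.40/27.40 = RR 1.0365; for all women it is 19.17/18.17 = RR 1.0550. The required sizes (716,392 and 570,014) cannot be reproduced, because the R² values, BMI group shares and SD of gain are not given. They are plausible. Under the Signorini formula, two-sided, a BMI group holding 5% of nulliparous women needs 619,949 at R² = 0, so 716,392 implies R² = 1 − 619,949/716,392 = 0.135.

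**2. Algebra (no distributional assumption).** Let the log risk be a·pre + b·gain. Since delivery = pre + gain,

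a·pre + b·gain = a·delivery + (b − a)·gain.

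The gain RR is exp(b) given pre-pregnancy BMI and exp(b)/exp(a) given delivery BMI. The second equals 1 when b = a and is below 1 when b < a.

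**3. When delivery BMI wins.** With a linear predictor and gain uncorrelated with pre-pregnancy BMI, delivery BMI alone fits better than pre-pregnancy BMI alone when

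2ab + b²·(Var gain / Var pre) > a².

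With the SDs assumed in step 4 (gain 2, pre-pregnancy BMI about 6.4), the variance ratio is about 4/41 = 0.10. Writing r = b/a, 2r + 0.10r² > 1 gives r above about 0.49. So delivery BMI wins once a unit of gain matters more than about half as much as a unit of pre-pregnancy BMI.

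**4. Simulation in the protocol's form.** Taken from the protocol: 716,392 births, a 27.40% cesarean rate, six pre-pregnancy groups, delivery groups cut at the same quantiles, and a true gain RR of 1.0365. Assumed: median pre-pregnancy BMI 26.2 (log-SD 0.235), gain mean 4.7 and SD 2. Rows 2 and 3 span correlations of 0, −0.15 and −0.3; rows 1 and 4 use −0.3.

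| True RR per unit of pre-pregnancy BMI | b/a | Algebra: 1.0365 ÷ column 1 | AIC margin for delivery BMI | Gain RR, pre-pregnancy groups | Gain RR, delivery groups |
|---|---|---|---|---|---|
| 1.0202 | 1.79 | 1.016 | 672 | 1.034 | 1.016 |
| 1.0305 | 1.19 | 1.006 | 722 to 1,013 | 1.033 to 1.037 | 1.006 to 1.009 |
| 1.0365 | 1.00 | 1.000 | 911 to 978 | 1.035 to 1.036 | 1.001 to 1.002 |
| 1.0460 | 0.80 | 0.991 | 833 | 1.033 | 0.991 (z = −10) |

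AIC chose delivery BMI in all eight runs. Per unit of gain, the targeted +1 point becomes 27.40 × 0.016 = +0.44, 27.40 × 0.001 = +0.03, or 27.40 × (−0.009) = −0.25 points. Grouping delivery BMI did not prevent this. With the knot at 5, both spline terms moved the same way (0.991 and 0.990 in the last row).

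A second simulation used other assumptions: 700,000 births, pre-pregnancy mean 27 and SD about 6, gain mean 5 falling by 0.12 per BMI unit, residual SD 2.3. For pre-pregnancy log-RRs of 0.02, 0.03, 0.036 and 0.045, the gain RR given delivery classes was 1.016, 1.005, 1.000 and 0.993. AIC favoured delivery BMI by 854 to 1,223.

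**5. Weaker gain effects (step 4 setting, correlation −0.3).**

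| True gain RR | True pre-pregnancy RR | b/a | AIC picks | Gain RR the plan would report |
|---|---|---|---|---|
| 1.0181 | 1.0460 | 0.40 | pre-pregnancy, by 390 | 1.014 |
| 1.0151 | 1.0305 | 0.50 | pre-pregnancy, by 74 | 1.012 |
| 1.0000 | 1.0305 | 0 | pre-pregnancy, by 721 | 0.997 |

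Here the primary analysis gives the gain effect given pre-pregnancy BMI, and the problem does not arise.

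**The case against.** The strongest defence is that the protocol never states a total effect of gain as its estimand. Its aim is descriptive, and comparing the two BMI measures is part of the objective. The Background raises the possibility that "gestational weight gain may not be associated with cesarean delivery independently of BMI at the time of birth", and gain conditional on delivery BMI is the quantity that addresses this. A null value there has meaning: a unit gained carries the same risk as a unit carried before pregnancy, so final BMI summarises both. This stands. The delivery-adjusted estimate is a legitimate second quantity, not a mere artefact. It justifies reporting both estimates, but not letting AIC decide which becomes the headline under one name.

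It is also fair that RR 1.0365 is an effect the protocol wants to be able to detect, not one it expects, and that the BMI and gain distributions above are assumptions. They affect the size of the change, not the algebra.

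Stronger readings do not hold:

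- A reader might infer that the plan always cancels the gain effect. Step 5 shows otherwise.
- A reader might infer that with no true gain effect the primary analysis would report a spurious protective RR of about 0.97. The delivery-adjusted model does give that (0.970 and 0.971 in the two simulations). At that point, however, AIC selects pre-pregnancy BMI, so the primary plan would not fit that model. The mechanism remains relevant only where delivery BMI is fixed, and those models have other outcomes.
- A reader might infer that the sample size is wrong. Its R² values use pre-pregnancy BMI only, so the delivery-BMI branch was not covered, but no corrected number follows.

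**Conclusion.** The point holds in this form. An AIC comparison of models without gain determines whether the primary gain RR estimates b or b − a, so the data choose the meaning of a primary-objective estimate. That follows from the definition of gain alone.

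The size depends on assumptions. When gain's per-unit effect exceeds about half that of pre-pregnancy BMI, AIC tends to select delivery BMI. A true gain RR at the protocol's target of 1.0365 can then appear as about 1.00 to 1.02, or reverse to about 0.99. Below that ratio AIC mostly selects pre-pregnancy BMI and the estimate keeps its ordinary meaning. The planned sensitivity analyses would not reveal which case applies. The laceration and trial-of-labour models carry the b − a meaning regardless, and they contradict the plan's own selection rule.

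**What to change.** - Prespecify pre-pregnancy BMI as the adjustment variable for the headline gain RR in the primary, subgroup and secondary models, including laceration and trial of labour.
- Keep the AIC comparison of pre-pregnancy and delivery BMI as a stand-alone answer to the second part of the objective. It should not feed any later model.
- Report the gain RR adjusted for delivery BMI as a labelled secondary quantity: a unit gained versus a unit carried before pregnancy. State that a null value there is not evidence that gain has no effect. This keeps the contrast the Background asks about.
- Do not replace that contrast with a comparison of pre-pregnancy BMI plus gain against delivery BMI alone as a test of b = a. With categorised BMI these models are not nested, so the comparison is not a direct test.

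Cost: protocol wording and a few extra fits on the same public data. No new data are needed.

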### Primary outcome

Rate of cesarean delivery

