### Sample size

To estimate R^2^, pre-pregnancy BMI group and BMI gain were regressed on the other explanatory variables using equivalent US birth data for the preceding year (2022). As pre-pregnancy BMI was categorized according to IOM groups, dummy variables were created with normal BMI (18.5 to < 25) as the referent category, and each of these was regressed on the remaining dummy variables, the two BMI gain spline variables, and the other explanatory variables, resulting in five R^2^ estimations. As BMI gain was a linear spline with one knot, the two BMI gain spline terms were regressed on the five BMI group dummy variables, the remaining BMI gain spline variable, and the other explanatory variables, resulting in an additional two R^2^ estimations. These R^2^ estimations were repeated for nulliparous women only, resulting in 14 R^2^ estimations in total.

We specified an alpha value of 0.05 and beta value of 0.10, and a cesarean section rate of 18.17 % at the mean gestational BMI gain based on US birth data for 2022. This cesarean section rate was 27.40 % for nulliparous women only. We aimed to detect an increase in the cesarean section rate of one percentage point for each BMI category compared with the referent category (18.5 to < 25) (e.g., relative risk 19.17 %/18.17 %), and an increase in the cesarean section rate of one percentage point per kgm^-2^ of BMI gain. R^2^ values were used to calculate the variance inflation factor using the method described Signorini (1991) for calculating the sample size based on an exact Poisson Regression [19]. These calculations were performed using the pwrss package (Version 0.3.1) in R (Version 4.4.0).

The largest sample sizes required were:•For the full sample including nulliparous and parous women: required sample size = 570,014•For nulliparous women only: required sample size = 716,392

Based on the numbers of births in the 2022 data, we expect there will be enough births in the 2023 data to meet these required sample sizes

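### The log-likelihood test of pre-pregnancy against delivery BMI has zero degrees of freedom, and the likelihood ratio tests named for imputed data use a Poisson likelihood that is too conservative for a yes/no outcome

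*Protocol article*

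**What the plan says.** All references are to the protocol article.

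- **Outcome.** Under Primary outcome it is "Rate of cesarean delivery", a yes/no event for each birth, modelled by robust Poisson regression.
- **The two BMI models (Analysis plan).** The first has pre-pregnancy BMI and the covariates, without BMI gain. For the second, "Maternal BMI at the time of delivery will be modelled on the same covariates". Then "the model with the lowest Akaike Information Criterion (AIC) will be used to select the BMI variable with the greatest explanatory power", and the choice carries into the later analyses. The next comparison is: "The two models will also be compared using the log-likelihood test". The test is not defined further.
- **BMI classes.** Pre-pregnancy BMI has six classes. Sample size confirms the coding: "the two BMI gain spline terms were regressed on the five BMI group dummy variables". Delivery BMI is cut at the same quantiles, so it also has six classes.
- **Tests of variables.** In the paragraph on multiple imputation: "P-values for the likelihood ratio test for each variable in each imputed dataset will be pooled using the median p-value rule". For the primary outcome, "backward stepwise Robust Poisson Regression will be used", with no test or threshold named. Interactions of parity with BMI and with BMI gain are tested, again by an unnamed test, and can restrict the primary analysis to nulliparous women.
- **Objective.** The end of Background makes the comparison of the two BMI measures as predictors part of the primary objective.

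**The concern.** There are two separate problems.

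First, a likelihood ratio test needs one model nested in the other and a positive difference in parameter count. The two BMI models meet neither condition. Apart from the AIC ranking, this test is the only comparison the plan names for that part of the primary objective. The investigators would have a winner, but no p-value and no statement of how certain or how large the advantage is.

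Second, robust Poisson regression uses the Poisson likelihood only as a working device. The sandwich variance repairs standard errors and Wald tests. It leaves the log-likelihood, and any test built on it, as though the variance of a yes/no outcome were p rather than p(1−p). The resulting tests are too conservative and can contradict the robust confidence intervals reported beside them.

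**Working it through.** The plan states no figure for either comparison, so there is none to reproduce.

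**1. Degrees of freedom of the BMI comparison**

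Inputs: six classes, hence five dummies, for each BMI measure (Sample size; Analysis plan), and identical covariates (Analysis plan).

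- Let q be the number of other parameters. Each model has q + 5, so the difference is (q + 5) − (q + 5) = 0.
- Neither set of dummies is a special case of the other, so the models are non-nested. There is no chi-square reference distribution.
- AIC = 2k − 2 log L. With equal k, AIC(delivery) − AIC(pre-pregnancy) = −2 [log L(delivery) − log L(pre-pregnancy)]. Twice the log-likelihood difference is therefore the AIC difference with its sign reversed.

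In simulated data (n = 20,000 per set; BMI distribution, gain and slope assumed), twice the difference was −5.94, +18.98 and −7.71 in the first three sets. The AIC differences were +5.94, −18.98 and +7.71. A negative value cannot be a likelihood ratio statistic for nested models.

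**2. Does the Poisson likelihood upset the AIC choice?**

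In 40 such data sets, Poisson and Bernoulli AIC chose the same BMI measure 40 times. In the first three sets the Poisson gap was the smaller (for example 18.98 against 24.14 for the Bernoulli likelihood), but the winner did not change.

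**3. True size of a Poisson likelihood ratio test on a yes/no outcome**

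Inputs: p = 18.17% (all women) and 27.40% (nulliparous), both from Sample size; nominal level 5%.

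Under the null, the statistic behaves approximately as (1 − p) times a chi-square variable. The true size is therefore P(χ²_df > c_df / (1 − p)), with c_1 = 3.8415, c_2 = 5.9915 and c_5 = 11.0705.

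| df | p = 18.17% (1 − p = 0.8183) | p = 27.40% (1 − p = 0.726) |
|---|---|---|
| 1 | P(χ² > 4.694) = 0.030 | P(χ² > 5.291) = 0.021 |
| 2 | P(χ² > 7.322) = 0.026 | P(χ² > 8.253) = 0.016 |
| 5 | P(χ² > 13.529) = 0.019 | P(χ² > 15.249) = 0.009 |

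Simulated check for 1 df (4,000 replicates of n = 2,000; one binary covariate with an assumed prevalence of 30%):

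| Test | p = 18.17% | p = 27.40% |
|---|---|---|
| Poisson likelihood ratio | 0.032 | 0.023 |
| Binomial likelihood ratio | 0.049 | 0.048 |
| Robust Wald | 0.048 | 0.049 |

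**4. Loss of power**

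Take a 1-df effect with 90% power under a correctly sized two-sided 5% test. The expected z is 1.960 + 1.282 = 3.242. The Poisson test in effect requires 1.960/√(1 − p):

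- p = 18.17%: Φ(3.242 − 2.167) = 0.86
- p = 27.40%: Φ(3.242 − 2.300) = 0.83

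**5. Where the tests disagree**

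For 1 df, a Poisson likelihood ratio test and a robust Wald test at 5% reach different decisions only when the robust p-value lies between about 0.030 and 0.05 (all women) or 0.021 and 0.05 (nulliparous). The parity interactions would have 5 df (BMI classes) and 2 df (the two gain spline terms). In the full sample the nominal 5% level would be about 1.9% and 2.6%.

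**The case against.** The strongest reply is that the faulty test decides nothing. AIC selects the BMI variable, AIC is legitimate for non-nested models, and the log-likelihood comparison is an addition. That stands. A reader might infer that the plan will select the wrong BMI measure because its likelihood is wrong. Neither the documents nor the simulations support this.

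It can also be said that the article leaves the test undefined, and that the objective promises a comparison rather than a hypothesis test. Both are true. Zero degrees of freedom follows from the ordinary meaning of the term, and a Vuong-type test would escape it. But no such test is mentioned, and a comparison that the plan does name should be one that can be carried out.

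On the variable tests, a reader might infer that every elimination step and the parity decision use the Poisson likelihood ratio test. The text does not say so. That test is named only in the paragraph that applies if data are imputed, and the complete-case test is not named. Extending it to the other steps is plausible but conditional.

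A further reply is that the error runs in one direction and is small in practice. This also largely stands. BMI and BMI gain are protected from elimination, so only borderline covariates or interactions could be affected. At the required 570,014 to 716,392 births, strong effects will rarely be missed.

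Finally, one might argue from this that backward elimination should be abandoned. That does not follow: robust Wald tests work within it.

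**Conclusion.** The point holds in two limited parts and should be fixed.

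- The log-likelihood test, read as a likelihood ratio test, has 0 df and adds nothing to AIC. The BMI comparison in the primary objective keeps an acceptable ranking but has no usable test or measure of uncertainty.
- The likelihood ratio test named for imputed data is conservative. At a nominal 5%, its size is about 3.0% (1 df) or 1.9% (5 df) at a cesarean rate of 18.17%, and 2.1% or 0.9% at 27.40%. If the same test serves backward elimination or the parity decision, those steps inherit the problem for borderline terms only.

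The sizes rest on the plan's own cesarean rates and on the approximation of one common p; risk will vary between women, so they are approximate. The agreement of the AIC rankings rests on assumed BMI distributions and effects. No shift in any BMI relative risk has been shown.

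**What to change.** 1. Delete the sentence on the log-likelihood test. Keep AIC as the selection rule. Report the difference in predictive performance between the two BMI models (for example Bernoulli log score or c-statistic) with a bootstrap 95% confidence interval. Alternatively, name a Vuong-type test for non-nested models.
2. Replace the likelihood ratio test for each variable with a robust multi-parameter Wald test. Name that test for the covariates in backward elimination and for the parity interactions.
3. If data are imputed, pool the Wald tests by Rubin's rules in place of the median of likelihood ratio p-values.

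The cost is a few changed sentences, a few lines of code and some computing time for the bootstrap on several hundred thousand births. No design feature or data requirement changes.

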### Variables

Mean and standard deviation (SD) will be used to describe continuous variables if they are normally distributed, otherwise median, and interquartile range (IQR) will be used. Categorical variables will be reported as numbers and percentages.

Gestational BMI gain in kgm^-2^ will be reported in the primary analysis. GWG in kg will be analysed for the sensitivity analysis.

Variables will be measured/described as follows:-Gestational BMI gain in kgm^-2^ (for the main analysis). Analysed as a linear spline with a knot at 5 kgm^-2^ based on preliminary analysis of 2022 data.-Self-reported pre-pregnancy BMI in kgm^-2^ (based on height and self-reported pre-pregnancy weight) classified according to the Institute of Medicine (IOM) groups [15]-Measured BMI at birth in kgm^-2^ classified into groups of the same size as pre-pregnancy BMI to account for expected weight gain during pregnancy-GWG in kg (for the sensitivity analysis)-Parity (categorized as nulliparous, or parous)-Maternal age in years (as a continuous variable, with linearity observed in the preliminary analysis of the 2022 data)-Gestational age at birth in weeks (categorized by gestational week)-Maternal height in cm (as a continuous variable, with linearity observed in the preliminary analysis of the 2022 data)-Maternal race (to be categorized as the dataset allows)-Maternal cigarette smoking during pregnancy (to be categorized as the dataset allows)-Payment type (public/private)-Trimester of onset of maternity care (first/second/third trimester/no antenatal care)-Maternal education (categorized as (i) 8th grade or less, (ii) 9th-12th grade, no diploma, (iii) completed high school or GED, some college credit or associate degree, (iv) bachelor’s degree, (v) masters degree, doctorate or professional degree)-Any fertility treatment used in conception (yes, no, unknown)-Diabetes in pregnancy (to be categorized as the dataset allows)-Hypertensive disorders in pregnancy (to be categorized as the dataset allows)-Previous preterm birth (yes, no)

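### Adjusting for maternal BMI only in six classes leaves residual confounding in the two BMI-gain slopes that can match or exceed their standard errors at this sample size

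*Protocol article*

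**What the plan says.** Under Analysis plan, "Pre-pregnancy BMI will be categorized according to the United States Centers for Disease Control and Prevention", giving underweight, normal, overweight and three obesity classes, the last open-ended. Delivery BMI is "classified into groups of the same size as pre-pregnancy BMI", using the same quantile cut-offs. Whichever of the two gives the lower AIC becomes the maternal BMI term in every later model. BMI gain is a linear spline with one knot at 5 kg/m², so its effect is two slopes. Maternal age and height stay continuous after a linearity check on 2022 data.

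The Sensitivity analysis section lists two analyses: weight gain in place of BMI gain, and complete cases in place of imputed data. Neither uses continuous BMI.

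The Background reports that "GWG decreased with increasing BMI" and that the risk of adverse outcomes rose with BMI. The Sample size section targets "an increase in the cesarean section rate of one percentage point per kgm^-2^ of BMI gain".

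**The concern.** Class indicators remove differences in BMI between classes but not within them. The Background supplies both links needed for confounding, BMI to gain and BMI to outcome. Inside a class, a woman with lower gain tends to have a higher BMI, and the gain slopes absorb part of the BMI effect. The main confounder of gain is thus modelled more coarsely than age, height or gain itself.

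Describing the relation between BMI gain and cesarean delivery is the first half of the primary objective. The motivating idea is close to a null: that gain may add nothing once BMI at birth is accounted for. With several hundred thousand births the standard errors are very small and shrink with N, while this bias does not. A small systematic error can then pull intervals off their target and make a null gain effect look significant.

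**Working it through.** **Inputs from the protocol (Sample size).** "We specified an alpha value of 0.05 and beta value of 0.10". "a cesarean section rate of 18.17 % at the mean gestational BMI gain". "This cesarean section rate was 27.40 % for nulliparous women only". Required N is 716,392 (nulliparous) and 570,014 (all women). One percentage point per kg/m² in nulliparous women is RR 28.4/27.4 = 1.0365, log RR 0.0358.

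**The plan's own N.** Signorini: N = [z(1−α/2)√V0 + z(1−β)√V1]² / [rate × (log RR)² × (1−R²)]. The R² values and class shares are not reported, so 716,392 can be neither confirmed nor refuted. It is plausible for a small class. At 5% prevalence, two-sided, R² = 0, N = 619,949, and 716,392 needs R² = 1 − 619,949/716,392 = 0.135. N is taken as given below.

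**Assumptions (not in the protocol).** Log-normal BMI with median 26 (class shares about 8/36/29/17/7/4%); mean gain 4.8 kg/m² at BMI 27, falling linearly with BMI; gain SD 2.3; risk log-linear in BMI; no other covariates.

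**Method.** Robust Poisson with the planned gain spline and six classes was fitted to expected outcomes in 1,000,000 simulated women. The robust SE was scaled to N = 716,392 at 27.4% risk. With k = bias/SE, coverage = Φ(1.96 − k) − Φ(−1.96 − k). Joint rejection = P(χ²₂(λ) > 5.99), where λ = b′V⁻¹b for the two slope biases b with covariance V.

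**Pre-pregnancy classes**

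| BMI log RR per unit | Gain slope per BMI unit | k below knot | Coverage | k above knot | Coverage |
|---|---|---|---|---|---|
| 0.0072 | −0.10 | −0.3 | 94% | −0.2 | 95% |
| 0.02 | −0.10 | −1.0 | 84% | −0.5 | 92% |
| 0.03 | −0.06 | −0.9 | 84–86% | −0.5 | 92–93% |
| 0.03 | −0.10 (mid-case) | −1.6 | 64–65% | −0.7 | 89% |
| 0.04 | −0.10 | −2.5 | 31% | −0.9 | 83–86% |
| 0.04 | −0.13 | −3.2 | 10% | −1.2 | 79% |

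The 0.0072 row spreads the one-point class difference in the Sample size section over five BMI units: 0.0358/5.

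Mid-case by hand, below the knot: bias −0.0025, SE 0.00152, k ≈ −1.6, coverage Φ(3.56) − Φ(−0.36) = 0.9998 − 0.3594 = 0.64.

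**Zero gain effect.** The mid-case estimates are −0.0026 below and −0.0011 above (k −1.79 and −0.63; coverage 57% and 90%). Over log RR 0.02–0.04 and slopes −0.06 to −0.13, the joint test rejects in 10% to 94% of studies, mid-case about 47%, against a nominal 5%. The mid-case figure moves with the set-up; another run of it gave 36%.

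**Other settings.**
- Gain SD 1.8 or 2.8 instead of 2.3, in the 0.04/−0.10 case: k below the knot −3.4 or −1.9.
- Assumed N of 1,100,000, mid-case: k −2.1 below, −0.9 above.
- Full sample, N = 570,014 at 18.17%, log RR 0.03–0.04, slopes −0.06 to −0.10: k −0.6 to −1.6 below, −0.3 to −0.6 above.
- Delivery-BMI classes with risk driven by delivery BMI, gain SD 2.3: k −0.3 to +1.3, mostly positive, joint rejection 5% to 43%. Letting the gain SD vary widens k below the knot to −1.4 to +1.8.
- Continuous, correctly specified BMI: bias zero by construction.

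**Absolute size.** The largest bias is about 0.006 in log RR per kg/m², so the RR is off by about 0.6%, or 0.006 × 27.4 ≈ 0.16 percentage points against a target of one. In the mid-case, a true RR of 1.0365 would read about exp(0.0358 − 0.0025) = 1.034.

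**The case against.** The strongest reply is that this does not change a conclusion. The error is a small fraction of the target effect, and at this sample size almost any mild misspecification, including error in self-reported weight, can exceed a standard error. That stands for the point estimate. It does not answer the coverage problem, or the test of a null that the Background itself raises.

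Second, every input that drives the size lies outside the document, and the simulation has no other covariates. Adjusting for diabetes and hypertension would probably absorb part of the BMI gradient and shrink the bias. This stands, and is why the result is given as a range. The 0.0072 gradient, where the bias vanishes, comes from a minimum detectable difference and is not an expected gradient.

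Third, a reader might infer that the bias is always several standard errors, that the interval misses the truth, and that gain will always look falsely protective. The documents do not support this. Such figures arise from one straight-line gain term, whose SE is √[0.726/(0.274 × 716,392)]/2.2 ≈ 0.0009 with a gain SD of 2.2. The planned spline slopes have SEs of about 0.0013–0.0021. Nor is the direction fixed. The plan may select delivery BMI, which contains the gain; the bias is then mostly positive, and the gain slopes also change meaning.

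Finally, the class contrasts are themselves a stated target, so the classes have a place. The fix keeps them.

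**Conclusion.** The point holds in a limited form. Six-class adjustment leaves within-class confounding in the BMI-gain slopes, and no listed analysis would reveal it. Under the stated assumptions with pre-pregnancy classes, nominal 95% intervals can under-cover, mainly below the knot, and a joint test of no gain effect can reject too often. Three SE or more at the stated N appears only below the knot, and only with a steep BMI gradient combined with a strong gain slope or a small gain SD. The size depends on the BMI gradient, the gain slope and the gain SD, which the 2022 data could supply. This concerns coverage and the test of a null gain effect. It is not evidence of a materially wrong RR.

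**What to change.** Keep the six classes for the table of class-specific RRs. Estimate the BMI-gain spline RRs from a model in which the selected maternal BMI enters as a continuous restricted cubic spline (for example five knots at fixed percentiles), and name that model as primary for gain. At a minimum, add it to the Sensitivity analysis section. Compare pre-pregnancy and delivery BMI by AIC in the same continuous form.

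The cost is a change of wording and one more model fit. The downside is that class RRs and gain RRs then come from two models, which the report should state.
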